## Abstract

**Background:**

Spinal cord injury (SCI) is a devastating condition with limited therapeutic options despite decades of research. Current treatment options include use of steroids, surgery, and rehabilitation. Nevertheless, many patients with SCI remain disabled. MLC601 (NeuroAiD), a combination of natural products, has been shown to be safe and to aid neurological recovery after brain injuries and may have a potential role in improving recovery after SCI.

**Objective:**

The aim of this study is to evaluate the safety and efficacy of NeuroAiD amongst people who sustain SCI in the study setting.

**Methods:**

Spinal Cord Injury—Assessing Tolerability and Use of Combined Rehabilitation and NeuroAiD (SATURN) is a prospective cohort study of patients with moderately severe to severe SCI, defined as American Spinal Injury Association (ASIA) Impairment Scale (AIS) A and B. These patients will be treated with open-label NeuroAiD for 6 months in addition to standard care and followed for 24 months. Anonymized data will be prospectively collected at baseline and months 1, 3, 6, 12, 18, and 24 and will include information on demographics; main diagnostics; and neurological and functional state assessed by the Spinal Cord Independence Measure, ASIA—International Standard for Neurological Classification Spinal Cord Injury, and Short Form (SF-8) Health Survey. In addition, NeuroAiD treatment, compliance, concomitant therapies, and side effects, if any, will be collected. Investigators will use a secured online system for data entry. The study is approved by the ethics committee of Hospital University Kebangsaan Malaysia.

**Results:**

The coprimary endpoints are safety, AIS grade, and improvement in ASIA motor score at 6 months. Secondary endpoints are AIS grade, ASIA motor scores and sensory scores, Spinal Cord Independence Measure (SCIM), SF-8 Health Survey, and compliance at other time points.

**Conclusions:**

SATURN investigates the promising role of NeuroAiD in SCI especially given its excellent safety profile. We described here the protocol and online data collection tool we will use for this prospective cohort study. The selection of moderately severe to severe SCI provides an opportunity to investigate the role of NeuroAiD in addition to standard rehabilitation in patients with poor prognosis. The results will provide important information on the feasibility of conducting larger controlled trials to improve long-term outcome of patients with SCI.

**Trial Registration:**

Clinicaltrials.gov NCT02537899; https://clinicaltrials.gov/ct2/show/NCT02537899 (Archived by WebCite at http://www.webcitation.org/6m2pncVTG)

## Introduction

### Background

Spinal cord injury (SCI) is a devastating neurological disorder that affects thousands of individuals each year. Global incidence rate of traumatic SCI in 2007 was estimated at 23 cases per million (133,000 to 226,000 cases per annum) and prevalence was between 236 to 4187 per million [1].

Over the past decades, much progress has been made in our understanding of the molecular and cellular events in SCI, providing insights into important mechanisms of tissue damage and failure of regeneration of injured neurons. Current treatment options for SCI include the use of high-dose methylprednisolone and surgical interventions to stabilize and decompress the spinal cord in the acute period, while rehabilitation is provided as long-term management. There is currently no treatment that enhances recovery after the injury, and SCI remains to be a devastating condition for which therapeutic options are still limited [2].

Three decades of clinical research on interventions to improve neurological outcomes in persons with SCI has not translated the promise of preclinical discovery into a consensus standard of care treatment. Nonetheless, SCI researchers remain hopeful that advances in preclinical discovery coupled with improved clinical trial performance will yield effective restorative treatment [3].

There have been many lessons learned from past failures in clinical trials, including patient selection based on knowledge of prognosis for spontaneous natural recovery and other eligibility criteria, clinical trial design, and outcome measures [4-7]. By taking the lessons into consideration in selecting a series of cases to be treated, important insights may be gained into the potential role of NeuroAiD as a therapy for SCI.

MLC601 (NeuroAiD, Nu-rAiD) is a combination of 14 natural ingredients indicated as treatment for poststroke recovery widely used in China and in many countries in Asia [8,9]. In Europe, a simplified formulation of the product, MLC901 (NeuroAid II, NurAiD II), consisting of 9 herbal components is available and will soon be available in Asian countries as well. Both formulations shall collectively be referred to as “NeuroAiD” in this study.

NeuroAiD efficacy and safety are supported by preclinical and clinical studies. The neuroprotective and neuroproliferative properties of NeuroAiD have been extensively elucidated during in vitro and in vivo experiments using animal and cellular models of focal and global ischemia [8-11]. In addition, research on its positive effects in traumatic brain injury (TBI) has recently been published [12,13]. What are remarkable are the effects of NeuroAiD on neurogenesis and neurorestoration beyond mere neuroprotection.

Case series reports of the use of NeuroAiD in neurosurgical conditions have been the subject of publications and presentations in international neurosurgical congresses [14-16]. In addition, there are several ongoing studies on the use of NeuroAiD in poststroke cognitive impairment and TBI [17-19].

The clinical data on NeuroAiD, however, are most well-reported in stroke. A systematic review of randomized clinical trials on NeuroAiD showed its benefits in improving functional outcomes and neurological deficits with 3 months treatment among patients with ischemic stroke in the preceding 1 week to 6 months [20-25]. Subsequently, NeuroAiD was investigated in acute ischemic stroke within 72 hours of onset which demonstrated the treatment effect to be larger in postacute and relatively more severe stroke at 3 months [26-29]. The updated meta-analysis showed a pooled odds ratio in favor of NeuroAiD [27]. Furthermore, treatment with NeuroAiD was associated with a reduction in risk of early vascular events after a stroke [30]. More recently, the extension study of this randomized, placebo-controlled, double blind trial has provided evidence of its benefit on long-term functional outcome persisting over time up to 18 months after a stroke with an excellent safety profile [31].

Since 2001 when it was marketed in China, there have been minimal serious side effects reported to date with the use of NeuroAiD. The common side effects reported from NeuroAiD were mostly mild and transient. Excellent clinical safety has been demonstrated in published clinical trials which reported the more common adverse events being gastrointestinal (nausea, vomiting, discomfort, diarrhea, dry mouth) and headache [20-34]. Safety studies in humans have shown that NeuroAiD, given alone or combined with aspirin, had no effect on clotting and coagulation [35]. Furthermore, there was no effect on hematological, hemostatic, and biochemical parameters or electrocardiogram in normal and stroke patients, even when started within 48 hours of stroke onset [35-37].

### Study Objectives

The primary objective of this cases series is to evaluate the safety and potential role of NeuroAiD in SCI.

## Methods

### Study Design and Subject Eligibility

Spinal Cord Injury—Assessing Tolerability and Use of Combined Rehabilitation and NeuroAiD (SATURN) is a prospective cohort study of patients with moderately severe to severe SCI treated with open-label NeuroAiD in addition to standard care (Figure 1).

As this is an open-label study, inclusion of patients with SCI who are likely to spontaneously recover may confound the results of the study. Potential prognostic factors are severity of SCI and time from injury to assessment [4]. Therefore, patients are included in the study if they meet all of the following inclusion and none of the exclusion criteria (see Textbox 1).

**Figure 1 figure1:**
[figure not shown]
Spinal Cord Injury—Assessing Tolerability and Use of Combined Rehabilitation and NeuroAiD (SATURN) study flowchart.

Selection criteria for the study.Inclusion criteria:Male or femaleAge 18 to 65 yearsDiagnosed with SCI between 3 days and 4 weeksAmerican Spinal Injury Association (ASIA) Impairment Scale (AIS) A or BInformed consent obtainedExclusion criteria:Nonsurvivable injuryMultiple significant trauma (ie, significant intracranial and extracranial injuries including limb fractures) that would limit observation of recovery from spinal cord injuryOther conditions that would limit clinical assessment of outcomes (eg, dementia, demyelinating disease, autoimmune disease)Refusal of treatment or contraindication to NeuroAiD

### Study Setting and Recruitment of Participants

Information about the study will be disseminated to the hospital and department staff. Any potential subject referred to the study team will be prescreened for potential eligibility. Permission to approach the patient or their legal representative will be obtained from the primary physician. Participants who fulfil the eligibility criteria will be recruited while still in the hospital for treatment or rehabilitation within the specified time window from injury. Informed consent will be obtained from all participants after discussion of the nature, purpose, and potential risks of the study.

### Treatment

Each 400 mg capsule of MLC601 contains 9 herbal ingredients (extracts of *Radix astragali*, *Radix salviae miltiorrhizae*, *Radix paeoniae rubra*, *Rhizoma chuanxiong*, *Radix angelicae sinensis*, *Carthamus tinctorius*, *Prunus persica*, *Radix polygalae*, and *Rhizoma acori tatarinowii*) and 5 nonherbal components (Hirudo, *Eupolyphaga seu steleophaga*, *Calculus bovisartifactus*, *Buthus martensii*, and *Cornu saigae tataricae*). MLC901 contains only the 9 herbal extracts.

The product is available in capsule form and administered orally or the contents may be diluted in water and administrated via gastric tube. The dosage is 4 capsules 3 times a day for MLC601 and 2 capsules 3 times a day for MLC901. The treatment duration is 6 months.

The capsules should be kept sealed until opened for administration and stored below 30°C in a dry place. NeuroAiD is manufactured according to applicable control measures that ensure the consistency and quality of the product from batch to batch and adhere to good manufacturing practice. The active ingredients and finished product are subjected to full quality control testing for safety.

All participants are allowed to receive standard care and other therapies and treatments including, but not limited to, surgery, rehabilitation, and other types of care deemed appropriate and as prescribed by their physician. There is no restriction to the use of any other treatment as recommended by the treating physician although other treatments should be recorded in the database.

### Variables Collected

Subjects will undergo assessments at baseline and at months 1 (±7 days), 3 (±14 days), 6 (±14 days), 12 (±30 days), 18 (±30 days), and 24 (±30 days) (see Table 1). Information collected is meant to specifically address the objectives of the study.

**Table 1 table1:** Schedule of Spinal Cord Injury—Assessing Tolerability and Use of Combined Rehabilitation and NeuroAiD (SATURN) study procedures.

Information collected	Base-line	Month 1 ±7d	Month 3 ±14d	Month 6 ±14d	Month 12 ±30d	Month 18 ±30d	Month 24 ±30d
Demographics	X						
Diagnosis and medical condition	X						
Surgical history	X						
AIS^a^ grade	X	X	X	X	X	X	X
ASIA ISNCSCI^b^ worksheet	X	X	X	X	X	X	X
NeuroAiD treatment/compliance	X	X	X	X			
SCIM^c^		X	X	X	X	X	X
SF-8^d^ Health Survey	X	X	X	X	X	X	X
Concomitant treatments/therapies	X	X	X	X	X	X	X
Adverse events	X	X	X	X	X	X	X

^a^AIS: American Spinal Injury Association Impairment Scale.

^b^ASIA ISNCSCI: American Spinal Injury Association International Standard for Neurological Classification Spinal Cord Injury.

^c^SCIM: Spinal Cord Independence Measure.

^d^SF: Short Form.

Data collected at baseline immediately prior to or at the start of NeuroAiD treatment will include

Demographics data: date of birth, gender, ethnicityDetails of diagnosis of SCI: date of occurrence; spinal cord level; cause of spinal cord injury; magnetic resonance imaging, computed tomography, or x-ray results; presence of specific sequelae of SCI (eg, respiratory failure, pneumonia, circulatory problems, spasticity and muscle tone, autonomic dysreflexia, pain, bladder and bowel dysfunctions, sexual dysfunction)AIS grade (pre- and postsurgery if patient undergoes surgery)ASIA International Standard for Neurological Classification Spinal Cord Injury (ISNCSCI) worksheet (pre- and postsurgery if patient undergoes surgery)Motor subscores for each limb and total motor score based on ASIASensory subscores based on ASIAOther items in the ASIA ISNCSCI worksheetNeuroAiD use: date started and doseConcomitant medications and treatments including any surgical intervention (date performed), treatments administered (start date and stop date), and rehabilitation (ie, physical and occupational therapies [start date, stop date, location—rehabilitation center, home-based]).

Data collected from month 1 to month 24 will include compliance with intake of NeuroAiD, occurrence of any adverse event, Spinal Cord Independence Measure (SCIM), and Short Form (SF)-8 Health Survey, in addition to the other clinical assessments performed at baseline.

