### Statistical Consideration

The target number of participants for this exploratory cohort study is set at 30. Descriptive statistics will be used to summarize data. Outcome assessments will be compared to baseline and previous observations. Comparison with appropriate historical controls with the same AIS grading and timeframe will be performed [4]. Multiple variable analyses will be used to identify predictors of better outcome, when appropriate. Other analyses deemed appropriate by the investigators and statistical consultant will also be performed.

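### SCIM has no scheduled baseline assessment, so the planned comparison of outcomes with baseline cannot be carried out for this secondary endpoint

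*Protocol article*

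**What the plan says.** All places are in the protocol article.

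- **Variables Collected, Table 1.** The SCIM row is empty at baseline and marked at all six later visits. AIS grade, the ISNCSCI worksheet and SF-8 are marked at baseline as well as at every later visit; the SF-8 row reads "SF-8^d^ Health Survey X X X X X X X".
- **Variables Collected, baseline list.** It opens with "Data collected at baseline immediately prior to or at the start of NeuroAiD treatment will include". The items that follow include neither SCIM nor SF-8.
- **Variables Collected, follow-up list.** From month 1 to month 24 it names, after compliance, "any adverse event, Spinal Cord Independence Measure (SCIM), and Short Form (SF)-8 Health Survey, in addition to the other clinical assessments performed at baseline".
- **Study Endpoints.** SCIM is a secondary endpoint at months 1, 3, 6, 12, 18 and 24.
- **Statistical Consideration.** "Outcome assessments will be compared to baseline and previous observations". No outcome is exempted. A second comparison is also planned: "Comparison with appropriate historical controls with the same AIS grading and timeframe will be performed".
- **Abstract, Methods.** "Anonymized data will be prospectively collected at baseline and months 1, 3, 6, 12, 18, and 24". The same sentence goes on to list "neurological and functional state assessed by the Spinal Cord Independence Measure" among the content.
- **Discussion.** Neurological, functional and quality-of-life outcomes are said to be measured. SCIM is the instrument that best fits the functional domain.

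**The concern.** The analysis text plans a comparison that the visit schedule cannot supply for SCIM. Among the scored outcomes in Table 1, SCIM alone has no value before or at the start of treatment, and the article gives no reason for the difference.

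This is an uncontrolled cohort, and the article itself names spontaneous recovery as the confounder. Without a starting value, nothing can be said about how far a participant's function has moved since treatment began. A change measured from the first available SCIM would leave out whatever happened in the first weeks, whether early treatment effect or early spontaneous recovery. The gap is also hard to fill afterwards: under Data Collection the study forms are the source documents and no other medical record is required.

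**Working it through.** No sample-size, power or error-rate figure is involved. The check sets the schedule against the analysis text and then works out when the first SCIM falls.

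**1. Is the baseline gap real?**

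| Outcome | Baseline in Table 1 | In baseline list | Later visits in Table 1 |
|---|---|---|---|
| AIS grade | yes | yes | 6 of 6 |
| ISNCSCI worksheet | yes | yes | 6 of 6 |
| SF-8 | yes | no | 6 of 6 |
| SCIM | no | no | 6 of 6 |

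The six SCIM marks correspond one to one with the six SCIM time points under Study Endpoints. A mark lost from the row when the table was read is therefore an unlikely explanation. The Table 1 cell carries the argument. The follow-up sentence does not prove the gap alone, because it names compliance, adverse events and SF-8 in the same way and Table 1 marks all three at baseline.

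**2. What does the gap block?** Change from baseline at visit t is SCIM(t) − SCIM(baseline). The second term is scheduled for none of the 30 planned participants, so the change cannot be computed at any of the six visits. Comparison with a previous observation needs two SCIM values and is possible from month 3.

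**3. When is the first SCIM, counted from the start of treatment?** Inputs: month 1 with a window of ±7 days (Table 1) and a 6-month treatment course (Treatment). Assumptions: month 1 is about day 30, and 6 months is about 183 days.

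- Earliest: 30 − 7 = day 23; 23/183 = 13% of the course.
- Latest: 30 + 7 = day 37; 37/183 = 20% of the course.

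**4. When is it, counted from injury?** Input: entry 3 days to 4 weeks after diagnosis of SCI (selection criteria). Assumptions: that window is counted from injury, and treatment starts at entry.

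- Entry at day 3: first SCIM at 3 + 23 = 26 to 3 + 37 = 40 days after injury.
- Entry at day 28: first SCIM at 28 + 23 = 51 to 28 + 37 = 65 days after injury.

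A participant entering at day 28 is at baseline inside the 26-to-40-day range in which the day-3 entrant already has a SCIM, yet has none taken then. If the reason for the empty cell were that SCIM is uninformative so soon after injury, the schedule would not apply that reason consistently.

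**The case against.** The strongest reply is that the SCIM endpoint can be computed as defined. Study Endpoints sets it as a value at each visit; only the ASIA total motor score is defined there as improvement against baseline, and that score has a baseline. The conflict then rests on one generic sentence under Statistical Consideration, half of which (comparison with previous observations) SCIM can satisfy. This stands, and it limits the severity. It does not remove the conflict, since the sentence makes no exception.

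The abstract is weak evidence too. Its sentence also covers demographics, which Table 1 collects only at baseline, so it cannot mean every item at every visit. It should be worded to agree with the table, but it does not establish that a baseline SCIM was intended.

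A baseline value would also have limits. Early scores are likely to be low, and change from a pre-treatment value in an uncontrolled cohort would include all the spontaneous recovery. Nor need change be more precise than the raw score. With equal variances and correlation r between the two times, its variance is 2(1 − r) times that of the raw score. For assumed values of r this is 1.4 at 0.3, 1.0 at 0.5 and 0.8 at 0.6. These points temper the benefit; they do not make the planned comparison possible without the measurement.

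A reader might go further in three ways that the article does not support:

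- **Month 1 becomes the SCIM baseline.** Nothing in the article says so; no substitute reference is named.
- **The historical comparison fails.** It is planned on AIS grade and timeframe. AIS grade is collected at baseline, and SCIM values at matching times remain usable. Adjustment for initial SCIM is not planned.
- **A quantified loss of precision.** That would need a correlation the article does not give and an adjusted SCIM analysis it does not specify.

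**Conclusion.** The point holds in limited form. Table 1 schedules SCIM at six of seven visits, none of them before or at the start of treatment, while Statistical Consideration plans comparison with baseline for outcome assessments generally. Followed as written, that comparison is unavailable for SCIM in all 30 planned participants. The earliest within-patient value lies about 23 to 37 days into treatment, if month 1 is about day 30.

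Severity is moderate. SCIM is secondary. Its observed values and visit-to-visit comparisons from month 3 survive, and AIS grade, ASIA motor score and safety are untouched. A reader might call SCIM the only functional outcome and rate the gap higher. That is a fair inference from the Discussion, but the article does not say it, and the abstract groups SCIM with ISNCSCI and SF-8 under neurological and functional state.

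The SF-8 discrepancy is editorial: Table 1 already schedules it at baseline, and the baseline list merely omits it.

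**What to change.** 1. Mark SCIM at baseline in Table 1 and add it to the baseline list under Variables Collected, with the same timing as the other baseline data (immediately before or at the start of treatment), for participants still to be enrolled.
2. For participants already enrolled without it, report SCIM as observed values at each visit, do not label month 1 as baseline, and state under Statistical Consideration that the comparison with baseline does not apply to their SCIM.
3. Add SF-8 to the baseline list so that it matches Table 1, and word the abstract to agree with the table.

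**Cost.** One more short scale at a visit that already takes place, a page on the data-entry form, and an amendment approved by the ethics committee. The amendment section bars removal of basic data elements, not additions. Early scores will probably be low, and earlier enrollees will have missing baseline values. The Results section says recruitment was under way; if it has since closed, only items 2 and 3 can still be carried out.

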### Data Collection

The investigators or designated personnel must record all required participant data in their entirety to ensure accurate interpretation of data. An explanation must be documented for any missing data. Data will be collected through an online data entry system [38] which is compliant with the Health Information Privacy and Security Act. Contributors to the study will be provided secured access accounts with username and password. Paper report forms are available if online submission is not possible (eg, Internet downtime, computer malfunction, power outage) but online entry is the preferred mode of data collection. If paper forms are used, data must be written in a neat and legible manner using black or blue ballpoint pen to ensure the clarity of the reproduced copy of all completed forms which are signed and dated. The completed online or paper forms shall serve as the source documents. No other medical record or source document will be required for this study.

